# Background of the project?

The benefits of glasionomer fillings were shown in literature. Nevertheless, in Germany glasionomer fillings are not accepted to be permanent restorations for the adult population. The new developed material EQUIA® (*Fuji IX GP Extra* coated with *G-Coat Plus®* ) gives –regarding manufacturers expectations- a new opportunity because of a combination of adhesive linkage to the teeth, esthetic improvements and special coating. Other benefits are x-ray opacity, biocompatibility, low sensitivity to moisture, low shrinkage. The main benefit of the new material –regarding manufacturer’s expectations- is the increase of mechanical strength. A nano-filled coating (GC G-Coat Plus) protects the surface initially from erosion. The product is introduced under the rules of MPG into the German market and is CE certified.

# Aims of the Study

The aim of this prospective clinical trail as cohort study according to MPG phase IV is ethical proved at the Ethical Comitee of Greifswald University (BB/2009) registerd at the WHO (DRKS-ID: **DRKS00004220**)

- To compare the survival rate of EQUIA^®^ (*Fuji IX GP Extra* coated with *G-Coat Plus^®^)* further named as “**Equia**” on the one hand and GIC *Fuji IX GP^®^ fast* coated with *Fuji Coat LC^®^* further called as “**Fuji IX**” on the other hand as filling material in posterior teeth.
- To compare the wear characteristics of EQUIA^®^ and Fuji IX
- To evaluate the renew ability of EQUIA^®^ and Fuji IX

Hypothesis is that the survival rate of EQUIA^®^ will be better than Fuji IX.

# Dental Treatment

Dentists in participating dental offices were randomly recruited regarding SOP. They

confirmed participation regarding SOP. Recruitment procedure takes place in

randomly selected cities with more than 50 thousands and less than 250 thousand

inhabitants regarding SOP.

Contact during study:

OA [name]. [name] and N.N.

# Study Type

Double Blinded – randomized – prospective – investor – initiated clinical trail

# Duration

5 years after the recruiting of participating dentists in their own dental practice

(proposed period of recruiting: 0.5 y, proposed period of treatment of participants:

0,5 y). Yearly Follow-up: start point: first placed filling).

# Calculation of the participants

The calculation of the numbers of participants were done with „nQuery 4.0“ software

by [name]. [name].

As aim (dependent variables) were used

- Loss of filling (dichotomy variable), defined as fracture or crack of the filling
- Abrasion of the occluded filled surfaces (scaled variable)
- Wear abrasion of the occlusal surface (scaled variable)

When the sample size in each group (Fuji IX and Equia) is 440, an exponential

maximum likelihood test of equality of survival curves with a p= 0.050 two-sided

significance level will have 90% power to detect the difference between a Group 1

exponential parameter, .1 of 20 % 0.0201 (corresponding to a proportion of 30% after

60 months) and a Group 2 exponential parameter, .2 of 0.0268 (corresponding to a

proportion of 20% after 60 months and a constant hazard ratio of

0.0201/0.0268=0.75) 30 %. This assumes an accrual period of 12 months, a

maximum follow-up time of 60 months (five years), and a common exponential

dropout rate of 1%.

The calculation is based on all incorporated units (fillings), e.g. all possible units

(fillings). The homogeneity of the participants will be guaranteed by the recruiting

phase, which will use the following selection criteria: Only one (at most two)

restoration for each side is calculated for each patient. The restoration will be limited

to posterior teeth (premolars and/or molars).

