# Cut off points

The study will be suspended if recruitment of dentists will not reach the estimated

numbers per cities during 6-9 month.

The study will be suspended, if failure rate reaches more then 5% of the fillings in the

first year.

The study will be suspended, if response will be below 60% of the examination each

year in respect to the year before.

Not used materials will be sent back to GC.

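### The sample-size sentence gives each group two contradictory five-year figures, and its hazards would breach the protocol's own 5% first-year suspension limit

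*Protocol*

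**What the plan says.** All the inputs stand in one sentence of the Protocol, section Calculation of the participants. It starts from 440 fillings per group and a two-sided 5% test, and claims 90% power for the comparison of the two groups' rates.

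- The first group is described by "exponential parameter, .1 of 20 % 0.0201 (corresponding to a proportion of 30% after", the time point being month 60.
- The second group has a monthly hazard of 0.0268. Its five-year figure reads "proportion of 20% after 60 months and a constant hazard ratio of", and the ratio is put at 0.75.
- Another percentage for the second group comes directly behind that ratio: "0.0201/0.0268=0.75) 30 %. This assumes an accrual period of 12 months, a". Follow-up is then capped at 60 months and dropout is set at 1% on an exponential scale, with no time unit.

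The sentence does not say whether the proportions are survival or failure. The section Cut off points adds "The study will be suspended, if failure rate reaches more then 5% of the fillings in the"; the period it names is year 1. The figure of 440 per arm returns as the target in Recruitment of patients (2nd Stage), and 880 in total appears under Monitoring.

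**The concern.** Each group carries two percentages, and they are crossed: 20% and 30% for the group with the lower hazard, 30% and 20% for the group with the higher hazard. Both pairs cannot describe the same quantity. Read as survival, the 30%/20% proportions fit the hazards. Read as failure, the 20%/30% tags fit the order of the hazards but not their values.

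Power in a survival comparison comes from the number of failures, and the two readings differ about threefold in that number. This sentence is the only justification for 440 per arm. As it stands, a reader cannot tell which effect the trial is powered for. A null result could be misread as having had 90% power against a hazard ratio of 0.75.

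**Working it through.** **Inputs** (Calculation of the participants): n = 440 per arm; two-sided alpha 0.05; hazards 0.0201 and 0.0268 per month; accrual R = 12 months; total time T = 60 months; dropout 1%, unit not given. From Cut off points: 5% failure in year 1.

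**1. What the hazards mean.** With S(60) = exp(−60λ):
- exp(−60 × 0.0201) = 0.299
- exp(−60 × 0.0268) = 0.200

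So the printed proportions are survival, and 70% and 80% fail.

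**2. Reproducing the stated power.** With uniform accrual and dropout hazard e, the probability of an observed failure is

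P = λ/(λ+e) × {1 − [exp(−(λ+e)(T−R)) − exp(−(λ+e)T)] / [(λ+e)R]}.

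With e = 0.01 per month, P = 0.536 and 0.628. Expected failures are 440 × 0.536 + 440 × 0.628 ≈ 236 + 276 = 512. On the log-hazard scale, power = Φ(|ln HR|·√n / √(1/P₁ + 1/P₂) − 1.96):
- √(1/0.536 + 1/0.628) ≈ 1.86
- 0.2877 × 20.98 / 1.86 ≈ 3.24
- Φ(3.24 − 1.96) ≈ 0.90

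Other variance forms, including the test on the hazard difference, need 436 to 444 per arm for 90%. Schoenfeld's formula needs 508 failures. The stated arithmetic is therefore correct for the printed hazards with dropout of 1% per month.

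**3. The tags read as failure.**
- −ln(0.8)/60 = 0.00372 and −ln(0.7)/60 = 0.00594 per month
- HR = 0.626
- With e = 0.01 per month, P = 0.142 and 0.215, so failures ≈ 62 + 95 = 157 (Schoenfeld needs 192 for 90%)
- 0.469 × 20.98 / √(1/0.142 + 1/0.215) ≈ 2.88, and Φ(2.88 − 1.96) ≈ 0.82

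**4. Range over the unstated dropout unit** (power at 440 per arm; failures in brackets):

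| 1% dropout is | Printed hazards, HR 0.75 | 20% vs 30% failure, HR 0.63 | HR 0.75 with 30% failure in the worse arm |
|---|---|---|---|
| per month | 0.90 (512) | 0.82–0.83 (157) | 0.46 |
| per year | 0.94–0.95 (616) | 0.90 (197) | 0.55 |
| over 60 months | 0.95 (625) | 0.90–0.91 (200) | 0.55 |

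For 20% versus 30% failure, 90% power needs 543 to 559 per arm with monthly dropout, 434 to 446 with yearly dropout and 426 to 439 with 1% over the whole study.

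**5. First-year failure against the 5% limit.** With 1 − exp(−12λ):
- printed hazards: 21.4% and 27.5%, that is 4.3 and 5.5 times the limit
- 20%/30% failure at five years: 4.4% and 6.9%, equal-arm mean about 5.6%

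**The case against.** The strongest defence is that the calculation is internally sound. Hazards, proportions, ratio, sample size and power agree with one another, and only two loosely placed percentages do not fit. Some of their odd placement may come from text extraction. That does not remove the problem. Nothing shows the percentages themselves to be artefacts, and the conflict with the suspension limit does not depend on them.

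Four stronger readings are tempting, and the document does not support them.

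- *The trial has only 82% power.* This holds only if 20%/30% failure is meant and dropout is 1% per month. The monthly unit is inferred because it reproduces 440 for the printed hazards; it implies about 45% dropout over 60 months (1 − exp(−0.6) = 0.45). With yearly or whole-study dropout, the 20%/30% rates themselves give about 440 per arm and 90%. If every filling were followed for a full 60 months, monthly dropout would give about 85%.
- *The protocol expects 20% and 30% failure.* No expected five-year failure rate is stated outside the disputed sentence. The suspension limit is a limit, not a forecast.
- *The 5% limit confirms the low-failure reading.* It is close to that reading and far from the other, but a mean of 5.6% still exceeds it if the limit is applied to all fillings.
- *Power for a hazard ratio of 0.75 is really 46%.* The protocol never pairs that ratio with 30% failure. The figure only shows that the 90% claim for 0.75 does not carry over to a low failure level, and it ranges from 46% to 55%.

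**Conclusion.** The point stands as a contradiction between inputs, not as an arithmetic slip. The hazards assume 70% and 80% failure at five years, while the tags beside them make sense only as 20% and 30% failure. Under the printed hazards both arms would pass the suspension limit more than fourfold in year 1, so the trial would be suspended under its own planning assumption. That conclusion needs only the exponential model the protocol itself uses.

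The effect on power is conditional. It is 90% as printed with monthly dropout, and between about 82% and 90% if 20%/30% failure was meant, depending on the dropout unit. The loss is moderate because 20% versus 30% failure is a stronger hazard ratio (0.63) than 0.75. A reader might infer that the trial is too small and must enrol more. The document does not settle the inputs well enough to say so. These figures treat fillings as independent; clustering within patients and dentists was not examined here.

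**What to change.** Rewrite the sample-size sentence so that it:

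1. says whether the proportions are failure or survival at 60 months;
2. gives one set of proportions, hazards and hazard ratio that agree;
3. states the time unit of the 1% dropout;
4. restates the power at 440 per arm after a rerun (about 82% if 20%/30% failure and monthly dropout are meant, about 90% if dropout is yearly or over the whole study);
5. no longer gives a hazard ratio of 0.75 as the effect detectable with 90% power, unless 70% and 80% failure is truly assumed.

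Under either reading, reconcile the assumed rates with the 5% first-year limit in Cut off points. The printed hazards exceed it in both arms, and the 20%/30% rates exceed it in one arm and on average.

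The cost is amendment wording and possibly a less favourable stated power. No additional fillings are required.

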# Data Safety and Monitoring Committee

The cases will be pseudonymized (continuously counted according to a single main

list). The Data-Safety-and-Monitoring-Committee (DSMC) will guarantee the

abidance of randomization and quality assurance at the data acquisition and data

base. Every six months the DSMC will forward a half-year report. [name]. [name] was asked for serving as a DSMC member and gave a preliminary consent. A

second member of DSMC will be one of the members of our board of the community

medicine research net with expertise in statistical methodology.

# Pseudonyms

Each dental practice gets a pseudonym (ID-OFFICE), which is known by only one

member of the research/examiner team in Greifswald (keyholder). Opening of the

pseudonym can only be done by DSMC and the keyholder in a formal consent.

Subjects included in the cohort will get a pseudonym (ID-PROBAND) by the

participating dentist. The dentists are the keyholders for the patients personal data.

The list of pseudonyms and patients´ ID will remain in the dental office. Only the

dentists (keyholder) could open the pseudonyms in their (private office) dental office.

The pseudonyms of ID-OFFICE and ID-PROBAND will allow complete data

calculation regarding the aims of the study.

# Recruitments

The recruitments of the dentists will be carried out in a two-stage design. Dentists will

be selected in a randomized design before the clinical trial will start.

The main project will start definitely after finishing the recruitments of dentists and

evaluation by the DSMC. In the dental practices patients will be recruited for the

study by a randomized list.

## Recruitment of dentists (1st Stage)

German cities of 50-250T inhabitants will be identified and 8 randomly selected.

The dentists will prepare the tooth and place the filling in the selected dental practice

regarding given manufactures recommendations; Dental practices will be randomly

selected in cities of more then 50 to 250T inhabitants. A short proposal will be sent to

30 randomly selected dental offices in each of the cities. Mailing to further dental

offices will be continued till 10 dentist per city confirmed participation.

Participating dentists will sign a short contract form and will be educated in the

sufficient application of GIC according to the manufacturers’ instruction and

according to GMP by GC including a training about the needed procedures written in

the SOP regarding the special research methods used in this study.

## Recruitment of patients (2nd Stage)

The patients are visitors of the cooperating dental practice, where the indication of

fillings in posterior teeth is indicated. A starting date will be given to the dentist, to

define when to start recruitment of patient by a randomized list. All participants, who

are randomly selected, will sign a consent form. If a patient is not willing to

participate, he/she will be asked along a short form of questionnaire (3 Items:

education, dental attendance, last visit of a dentist). Afterwards the list switches over

to the next random number.

The calculation of the fillings (see point 7) per participant (dentist and patients) in

different cities can be estimated by the mean of 1 to 3 fillings per patient (Mean 2)

and 3 to 8 patients (mean 5.5) per office, which were treated by 8 dentist in 10 cities.

In the study can be included 240 fillings at minimum, in the max 1920 fillings can be

calculated. If the number per dentist will not reach estimated mean, further dentists

will be recruited by the randomized design.

|  | filling/patient | patients/dentist | dentists/city | cities | expected | recommended |
| --- | --- | --- | --- | --- | --- | --- |
| **min** | **1** | **3** | **10** | **8** | **240** | **440 each arm** |
| **max** | **3** | **8** | **10** | **8** | **1920** |  |
| **mean** | **2** | **5,5** | **10** | **8** | **880** |  |

This calculation requires a continuously calculation of the included fillings in the study, to give a contemporary feedback to the participating dentist.

Additional cohorts (such as “GC opinion leaders”) are not included in this randomized

controlled study (RCS), but they can be added as “additional selected” cohorts

(ASC). They will be calculated separately and used as additional information for

discussion.

# Participants

Dentate patients attending the dental office, where the indication of a filling (amalgam

or composite) in the posterior region is given and who signed the consent form /

study contract (appendix).

## Inclusion criteria

Dentate patients (no partial or full dentures, proximately 3 opposing zones with

contact of natural teeth in the posterior region)

Fillings are limited to two surfaces (o, mo, od) but with one proximal cavity. The width of the cavity should not exceed 50% of the tooth distance and the approximal cavity width is limited to the cusp tip distance.

## Exclusion criteria

Patients with CMD dysfunction or malfunction (grating or articular crepitus, pressing)

will be excluded from the study. The entire screening method (CMD-Screening

according to DGZMK record) has been evaluated in previous research projects of the

study group (SHIP communication).

Participants, who may not be willing to sign the consent form, will be withdrawn to

take part in the clinical investigation (according to Declaration of Helsinki and

Guidelines ICH-GCP). Three questions will be ask for non-responder analysis and

sex and birthyear from patients data file will be noted instead of participation.

# Clinical Trial

Before patients will be included in this clinical trail, they must sign the consent form

and the acceptance of randomization. A Xerox of the patient consent form will be

given to the patient (participant).

The main list of randomization decides the treatment strategy and is oblique to be

included in the study. Patients which do not agreed with the randomization will be

excluded of the participance. The reason for withdrawal will be recorded (Question:

Which expectance did you established to the restoration material?)

According to indication, the cavity will be grained and an impression of the cavity

(Optosil) be undertaken. Ten questions regarding age, education, dental attendance,

oral hygiene, smoking etc. will be asked for the study record. The questions are part

of SHIP instrument (Study of Health in Pomerania, University of Greifswald).

The study box, handed out after the briefing lecture, contains blinded, numbered envelops, which contains only one single capsule. The use of this randomized material is binding. The capsule differs optically in the colour of the stamp. The colour code of the stamp shows, which coating (G-Coat LC or G-Coat Plus) has to be used in the last step. Is the necessity of an additional filling at the same volunteer indicated, the other study material will be used.

The filling will be placed according to manufacturers´ recommendations. To finish the

filling procedure, the surface has to be coated with G-Coat LC or G-Coat Plus (which

was used out of blinded, relabelled bottles by GC, Belgium) according to the random

list. Manufacturers´ recommendations and research methods will be trained before

(see above).

Regarding pseudonym procedure the patient will be registered by the next number in

the list and the envelope of randomization list will be opened to define the therapy

arm (G-Coat LC or G-Coat Plus). The bottles will be relabelled by “coat number A or

B”. The random list will tell the dentist to use bottle A or B. Only the project

management could identify the coat by the given numbers. So, neither the dentist nor

the participant will know in this blinded design which coat material was used.

*The materials get blinded and randomized by GC Europe. Only the information of the*

*expired date, colour (yellow, grey) is given to the participants.*

After cure of the material, the shape of the filling has to get contoured (diamant 10-20 µm) and sealed according to the manufactured recommendation.

Conserving the shape of the filling for the study a replica will be done by one phase A-silicone (EXA fast Injection, GC Company) and impression tray with a setting time of prox. 360 sec. The impression methods will be trained during education of filling procedures. Interocclusal records (interponates) will be done with Green-bite apple (Co: Detax, Germany) during baseline and the follow-ups in central occlusion.

The participant gets a unique pseudonym in the dental office. The unique pseudonym

remains in the list of the dental office.

The filling protocol/record with the randomized envelope number, Probands ID, setting date, treated tooth/teeth and surface has to be filled out. The impression gets named with the randomized envelope number and Probands ID. After all fillings are set, the filling record has to be send to the University Greifswald.

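### The rule for a patient's second filling conflicts with the single-capsule envelopes and the placement form, and lets the dentist choose which tooth gets which coded material

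*Protocol*

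**What the plan says.** All quotes in this field are from the Clinical Trial section.

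- **Supply:** "The study box, handed out after the briefing lecture, contains blinded, numbered envelops, which contains only one single capsule". The next sentence adds: "The use of this randomized material is binding".
- **Recognition:** "The capsule differs optically in the colour of the stamp", and "The colour code of the stamp shows, which coating (G-Coat LC or G-Coat Plus) has to be used in the last step".
- **Further fillings:** "Is the necessity of an additional filling at the same volunteer indicated, the other study material will be used".
- **Registration and masking:** The patient is registered under the next list number and an envelope is opened to define the arm. Coating bottles are relabelled A or B. Only project "management could identify the coat by the given numbers. So, neither the dentist nor" the patient is to know which coat was used.

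Recruitment of patients (2nd Stage) plans on one to three fillings per patient with a mean of 2, and its table reaches 880 fillings. Calculation of the participants limits restorations to one, at most two, per side. The Placement Protocol form in the Appendix has one row per envelope, and its worked example enters two teeth (15 and 16) in a single row. The follow-up record form has four treatment columns and no field for the material used.

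**The concern.** The allocation procedure for patients with more than one filling cannot be carried out as written. If every envelope holds one binding capsule, a second filling should take whatever the next envelope holds. If the second filling must take the opposite material, the next envelope will not always supply it.

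The stamp colour on the first capsule also settles the second allocation, yet no section says that the order of the teeth is fixed before the envelope is opened. A dentist facing two cavities of unequal difficulty could assign them after seeing the code, or include the second tooth only when its code suits. Neither act would break a written rule. The survival comparison is meant to be randomised, and it counts fillings, so this touches the primary aim. It concerns how material is assigned in the practice, which a separate analysis plan cannot repair.

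**Working it through.** **1. The plan's own figure.** Inputs are from the table in Recruitment of patients (2nd Stage): fillings per patient × patients per dentist × 10 dentists per city × 8 cities. The mean row gives 2 × 5.5 × 10 × 8 = 880, as stated. This equals two arms of 440 in Calculation of the participants.

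**2. Non-first fillings.** Each patient has one first filling, so the share is (fillings − patients) / fillings.

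| Row | Patients | Fillings | Non-first | Share |
|---|---|---|---|---|
| min | 3 × 10 × 8 = 240 | 240 | 0 | 0% |
| mean | 5.5 × 10 × 8 = 440 | 880 | 440 | 50% |
| max | 8 × 10 × 8 = 640 | 1920 | 1280 | 67% |

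**3. Second fillings only.** These are the ones fixed by the first capsule; a third filling is undefined rather than predictable. The protocol gives no distribution, so assume equal proportions p of patients with one and with three fillings, which keeps the mean at 2. Second fillings number 440 × (1 − p) and third fillings 440 × p.

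| Assumed p | Second fillings | Share of 880 | Third fillings |
|---|---|---|---|
| 0 (all have two) | 440 | 50% | 0 |
| 1/3 (one, two, three equally common) | 293 | 33% | 147 |
| 1/2 (half one, half three) | 220 | 25% | 220 |

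**4. Can both supply rules be followed?** The packing order is not stated, so take the possibilities in turn.

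- *Simple 1:1 random order (assumed):* the next envelope holds the same material with probability 0.5. Taking envelopes in sequence then fails the opposite-material rule for about half of second fillings.
- *Strict alternation:* the rule can be met, but every later allocation is predictable, first fillings included.
- *Random pairs:* this works only while each patient uses exactly two capsules. A patient with one or three leaves the next patient in the middle of a pair.

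**5. Against the form.** Two teeth in one envelope row does not fit one capsule per envelope. If the single capsule served both teeth, they would have the same material, contrary to the opposite-material rule. If it served one, the form shows neither which tooth that was nor where the second capsule came from.

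**6. What is left open.** No section gives the source of the other capsule, the tooth that takes the first capsule, or the material for a third filling.

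**The case against.** Much can be said in the plan's favour.

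- **Pairing is sound.** Opposite materials within a patient is a legitimate paired design: one random draw can allocate both teeth. This stands. The defect is the missing tooth order and the supply mechanism, not the pairing.
- **Cavity before capsule.** The Clinical Trial section describes preparing the cavity and taking its impression before it mentions the study box, so the first tooth may already be committed. That is narrative order, not a rule. It also does not prevent a decision about adding a second tooth.
- **Masking.** The dentist sees a code, not a product, and about 80 dentists (10 × 8) would have to lean the same way to produce a net bias. This stands as a limit on size and direction. It does not restore concealment, because two distinguishable codes are enough for selection.
- **Safeguards.** Cavity size is restricted and recorded, the data safety committee controls randomisation, and operating procedures not shown might set a tooth order. Even so, the envelope rule and the opposite-material rule would still conflict in the protocol.

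Three stronger readings are tempting but unsupported. First, a reader might infer that half of all fillings are predictably allocated; that counts third fillings, whose material is undefined. Second, a reader might infer that dentists open envelopes out of order and return known capsules. The protocol describes no such practice, and the eight-row form may mean that envelopes index patients, since eight is also the planned maximum of patients per dentist. Third, a reader might attach a biased hazard ratio. If one tooth of each pair has twice the hazard and 20% of pairs are steered one way, the ratio under no true difference is 1.4/1.6 = 0.875 within pairs. With 293 pairs it is (293 × 1.4 + 147 × 1.5) / (293 × 1.6 + 147 × 1.5) = 630.7/689.3 = 0.915 over all fillings. Both steering inputs are invented, and with no net direction the ratio is 1.0.

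**Conclusion.** The point holds as a contradiction in the allocation procedure with a resulting selection risk. The Clinical Trial section conflicts with itself and with the placement form, and it leaves three necessary rules unstated. A dentist following the text can choose, after seeing the first capsule, which tooth gets which code or whether a second tooth enters.

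The reach is 440 of 880 fillings as non-first at the planning mean, with second fillings at 25% to 50% under the assumed distributions. These figures show how many fillings the unclear rule governs, not how many are biased. Neither the size nor the direction of bias follows from the documents. The sample size is not affected.

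**What to change.** Keep the within-patient pairing and make it random and concealed:

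1. Before any envelope is opened, list all study teeth on the placement form in a fixed order, for example ascending tooth number. The first listed tooth takes the first capsule.
2. Supply material per patient as two sealed items, for the first and second listed tooth, with the two materials in random order.
3. Take third and later teeth, and any tooth first indicated after opening, from the next sealed pair in sequence.
4. Forbid taking envelopes out of order.
5. Reconcile the Clinical Trial section with the placement form so that envelope and capsule are recorded per tooth. The list then also shows any listed tooth that was not filled.

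The cost is repacking the study boxes, an added form line and some unused capsules. No extra patients are needed. Each patient with one or three fillings leaves one capsule over, so the waste is 440 × 2p: none if all have two fillings, about 293 at p = 1/3, and 440 at p = 1/2. Teeth indicated after opening would add to this.
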